### Recruitment

Primary participants will be recruited from 3 web-based platforms: Instagram advertising, Snapchat advertising, and the Student Edge panel. Specific details about each recruitment platform and how participants will be recruited are outlined below:

Instagram is a free-to-use photo and video sharing social network service predominantly used through smart phone apps. Instagram allows users to engage with a range of advertisements outside of their immediate social network. Instagram is currently owned by Meta, which administers Instagram’s advertising manager function. Using the advertising manager, businesses and users can manage paid advertisements on Instagram. The study will use the advertising manager to select target ages 16-18 years and limit the geographic area to Australia. The advertisement will feature images relating to the survey topics and text outlining the study. Tapping or swiping on the Instagram advertisement will direct prospective participants to the study information page.Snapchat is an instant messaging app that allows users to share pictures and videos (called “snaps”). Messages are usually only available to recipients for a short period before they can no longer be viewed. The study will use Snapchat’s paid advertising feature to select the target audience of people aged 16-18 years, within the geographic area of Australia. Paid advertisements in the form of a short video appear between viewing friends’ snaps, and people can swipe up to interact with the ad. The advertisement will feature a short, animated video with text outlining the study. By tapping on the advertisement, prospective participants will be redirected to the study information page.Student Edge [26] is a web-based organization targeted toward people in high school, technical and further education (TAFE), and university in Australia. The website provides students with study tips, news, promotions, competitions, job listings, and surveys. People can voluntarily sign up for the Student Edge Surveys panel to earn rewards. Student Edge will send an email invitation to prospective participants aged 16-18 years, who have signed up for their panel. Participants then click on the link in the email and are redirected to the study survey page.

Secondary participants are recruited by primary participants. When primary participants reach the end of the survey, a default message and URL unique to them and their friendship group will be generated. The primary participant is asked to discuss the project with their friends and share the message and URL. Secondary participants can click on the link to take them to the study information page and then proceed to the survey. One reminder email is sent to the primary participant 72 hours after they complete the survey. Secondary participants are not given the option to refer additional friends (ie, there is only 1 wave of secondary recruitment).

All participants will be required to provide their email address and mobile phone number. To prevent multiple responses from the same individual, repeat email addresses and mobile phone numbers will be detected by Research Electronic Data Capture (REDCap; Vanderbilt University), which is used to collect data (see below), and these participants will not be able to proceed with the survey.

### Allocation of Intervention

Primary participants are randomized upon opening the study webpage. Randomization is managed through a REDCap survey form to enable automatic allocation independent of the researchers. The timestamp when a participant opens the webpage determines their allocated group, with those opening at an even number of seconds assigned to the scaled group (intervention) and at an odd number of seconds to the fixed group (control). Primary participants are informed about their intervention group after they answer how many close friends they have. Secondary participants are assigned to the same intervention group as the primary participant who recruited them. Researchers will not be blinded to the intervention group as they have no direct contact with the participants.

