### Outcomes

The primary outcome is defined as the proportion of primary participants’ close friends who complete the survey. Survey completion is recorded if the secondary participant clicks the final survey submission button. This outcome measure indicates the level of complete data about each primary participant’s close friend network.

The secondary outcome is the number of close friends who complete the survey per primary participant. This outcome measure assesses whether the reimbursement model results in an overall higher number of participants.

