### Data Collection

Participants will complete a web-based survey using the REDCap data collection tool [27]. The survey will capture information about peer networks, mental health, alcohol and other drug use, COVID-19 vaccination, sexual health, social media, and media related to sexual health, including pornography, sexting, and dating apps. The survey begins with a study information webpage containing a brief video accompanied by written information explaining the purpose of the research, what is involved, and how to participate. After the study information, participants proceed to a sign-up or consent page. Participants provide their contact details (email and mobile number) and will be asked to complete a checkbox list indicating their informed consent to confirm they understand and agree to provide their information and the use of that information for the purpose of the study. Participants complete a 2-step authentication by entering a code sent to their nominated mobile number. Participants will then be directed to complete the survey. If the individual is a primary participant, a unique URL will be generated at the end of the survey to share with their friends.

The target peer networks for recruitment are assessed by asking primary participants about their close friends. Participants are asked how many people they consider to be their close friends and to give their initials or a codename for each. Participants proceed to answer questions about each friend’s age, gender, and perceived closeness. If participants have more than 10 close friends, they are asked to answer the questions for their 10 closest friends. Therefore, the possible range of nominated close friends who may be referred to as secondary participants is 0 to 10. A network size of up to 10 was deemed sufficient, as in other studies, most young people nominate only 2-3 close friends [9,27]. A limit was necessary to minimize the burden on participants to answer too many questions and manage the study’s budget for participant reimbursements.

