Potential factors associated with close friends completing the survey are collected through the web-based survey. Primary participant-level factors include primary participant demographic characteristics, recruitment settings (Instagram, Snapchat, and the Student Edge panel), and health outcomes and behaviors. Health domains include mental health and well-being, sexual health, social media use, technology use related to sex, alcohol, tobacco smoking, other drugs, and COVID-19 vaccination. Friend-level predictors include network size and close friends’ gender, age, perceived closeness, and frequency of discussing various health-related topics.

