### Data Management

Survey data for participants within the same peer network group will be linked using the unique auto-generated survey URL. Secondary participants’ survey data will be linked to the primary participants’ reported data using codenames and initials.

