### Statistical Analysis

All analysis will be conducted in Stata (version 15; StataCorp). We will first compare the 2 baseline groups to determine whether they are comparable on key demographic factors. If not, further analysis will be adjusted for any differences.

Our primary analysis will assess the effect of the reimbursement intervention on the proportion of primary participants’ close friends who complete the survey using a multilevel logistic regression model. In this model, close friend nominees are the lowest level of data and are grouped by primary participant. Each close friend nominee can either be successfully recruited or not recruited (a binary outcome).

For aim 2, to determine the effect of the intervention on the number of close friends per primary participant who complete the survey, we will use a regression model with a count distribution appropriate for the data.

In secondary analysis, we will identify factors associated with successfully recruiting each close friend by including friend-, relationship-, and primary participant–level variables. We will use a logistic regression model where the outcome is whether a primary participant successfully recruited at least one friend or recruited zero friends, and the potential predictors include recruitment setting, demographics, health variables, and network size.

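### Arm disclosure is tied to the friend count and not to a completed friend roster, so which friends are named as units of the primary analysis could depend on the arm

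*Protocol article*

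**What the plan says.** Allocation of Intervention puts randomization at the very start: "Primary participants are randomized upon opening the study webpage". The participant does not learn the arm then. The same section says: "Primary participants are informed about their intervention group after they answer how many close friends they have".

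Data Collection describes how the network is elicited: "Participants are asked how many people they consider to be their close friends and to give their initials or a codename for each". Each friend's age, gender and closeness follow. There is a cap: "If participants have more than 10 close friends, they are asked to answer the questions for their 10 closest friends".

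Three other statements show what the roster is used for:
- Outcomes: "The primary outcome is defined as the proportion of primary participants’ close friends who complete the survey".
- Statistical Analysis: "In this model, close friend nominees are the lowest level of data and are grouped by primary participant".
- Data Management: "Secondary participants’ survey data will be linked to the primary participants’ reported data using codenames and initials".

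The roster also supplies covariates for the secondary aim: "Friend-level predictors include network size and close friends’ gender, age, perceived closeness, and frequency of discussing various health-related topics".

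No section says whether the arm message is shown before or after the naming step, or whether earlier answers are locked once it appears.

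**The concern.** Because allocation takes place when the page opens, the timing of disclosure is the only thing that keeps the network measurement independent of the arm. The article ties disclosure to the count. A count fixes how many friends there are, but not which friends they are.

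If naming comes after disclosure, a participant in the scaled arm has just learned that each completing friend adds Aus $5 for everyone in the group, up to Aus $30 each. That participant may treat the roster as an invitation list and lean towards friends likely to take part. A participant in the fixed arm has no such prompt. Either arm might also name fewer friends than it counted.

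The trial asks what share of an existing close-friend network completes the survey. If the membership of the recorded network responds to the arm, the two proportions rest on differently selected friends, and a difference can appear without more of the true network being recruited. This would remain even if every primary participant finished the survey.

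**Working it through.** **Order of steps, from the text**

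1. Page opened and arm assigned (Allocation of Intervention).
2. Number of close friends answered (Allocation of Intervention; Data Collection).
3. Arm disclosed at some point after step 2 (Allocation of Intervention).
4. Initials or codename for each friend, then age, gender and closeness, for at most 10 friends (Data Collection).

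The article fixes step 3 after step 2. Its place relative to step 4 is inferred: the count is the named milestone, so the natural reading puts disclosure between count and naming. Data Collection, however, puts count and naming in one sentence, and disclosure after both would also fit the text.

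**The plan's own figures**

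The Sample Size section gives 0.2 per nomination in the scaled arm and a 2-fold difference, hence 0.1 in the fixed arm. It also gives 80% power, ICC 0.5, mean cluster size 3, and coefficient of variation 0.83. Two-sided 5% is assumed, because the article states no significance level.

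- Nominees per arm, independent: 199.
- Design effect: 1 + (3 − 1) × 0.5 = 2.
- Relative efficiency for unequal clusters: L = 1.5/(1.5 + 0.5) = 0.75; 1 − 0.83² × 0.75 × 0.25 = 0.871.
- Clusters per arm: 199 × 2/(0.871 × 3) = 152.3, rounded up to 153. The stated 153 reproduces.
- Effective nominees per arm: 153 × 3 × 0.871/2 ≈ 200.

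The sample size is sound on its own inputs and is not affected by this point.

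**Illustration A: incomplete naming, no true effect**

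Assume one arm names a fraction d fewer friends than it counted, all of them non-completers. Its apparent proportion is p/(1 − d), compared with p in the other arm, at about 200 effective nominees per arm.

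| d | p = 0.10 appears as | odds ratio | rejection rate | rejection rate at p = 0.20 |
|---|---|---|---|---|
| 10% | 0.111 | 1.13 | 6.5% | 8.5% |
| 20% | 0.125 | 1.29 | 12% | 22% |
| 30% | 0.143 | 1.50 | 26% | 52% |

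With the pre-disclosure count as denominator this disappears. At d = 20% and 3 counted friends, 0.3 expected completers over 2.4 named gives 0.125; over 3 counted it gives 0.10.

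**Illustration B: number fixed at 3, one friend replaced, no true effect**

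Assume a share s of the scaled arm replaces one friend (probability 0.10) with a keener one (probability q). The arm proportion becomes 0.10 + s × (1/3) × (q − 0.10).

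- s = 20%, q = 0.40: 0.10 + 0.20 × (1/3) × 0.30 = 0.12, ratio 1.2.
- s = 50%, q = 0.40: 0.15, ratio 1.5.
- s = 100%: 0.13 for q = 0.20, rising to 0.20 for q = 0.40.

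The planned ratio is 2. Using the count as denominator does not undo a replacement, since the number stays at 3.

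The values of d, s and q are all assumptions. The article gives no figure for any of them.

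**The case against.** The strongest reply is that the article never says the arm was disclosed before naming, and that the page order of a REDCap form is detail a condensed article may leave elsewhere. Moreover, what it does say is protective: the number of friends is answered first. This stands in part. The disclosure sequence must be read as probable, not established. But the article does fix a disclosure point, and the point it fixes does not by itself protect the roster.

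A second reply concerns incentive and opportunity. Payment follows recruitment through the shared link, and no section says it is checked against the named roster. With about 3 close friends expected, there is little room for substitution, and an explicit choice arises only for those with more than 10. This also stands: a motive to tailor the roster is conjecture about what participants believe.

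A third reply is that learning the arm hardly alters a friend's age or gender, and network size is answered beforehand. That is correct. Among the friend-level predictors, only rated closeness and discussion frequency are directly open to influence.

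A reader might go further and infer that the roster was completed after disclosure and that the result is therefore biased towards the scaled arm. The documents do not support this. The sequence is not stated, the behaviour is not documented, and the direction is not settled: replacement by keener friends would favour the scaled arm, but incomplete naming would favour whichever arm omitted more non-completers.

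**Conclusion.** The point holds conditionally. As worded, the protocol secures only the number of close friends before disclosure. If naming followed, the membership and completeness of the roster, the choice of 10, and the ratings of closeness and discussion frequency could all differ by arm, and the named friends are the units of the primary model. The planned baseline comparison of the two groups on key demographic factors is not aimed at the rosters.

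Size and likelihood are unknown. The illustrations show that modest arm-dependent naming could matter against a planned ratio of 2, but they do not show that it happened. If the form shows that naming came before disclosure, nothing remains beyond a clarifying sentence.

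**What to change.** **For any further use of the form:** reword the disclosure sentence in Allocation of Intervention so that the arm is shown only after the whole friend roster (names or codenames, the choice of 10, and all questions about each friend) is entered and locked. This costs one moved page and one sentence.

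**For this trial:** the Results section says recruitment is complete and analysis has not begun, so the form can no longer be changed but the analysis can still be fixed in advance.

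1. Confirm the actual disclosure point from the REDCap form.
2. If naming came first, state that in Allocation of Intervention. The concern then closes.
3. If naming followed disclosure:
   - use the pre-disclosure count, capped at 10, as the primary denominator, with counted but unnamed friends treated as not recruited;
   - compare by arm the number named against the number counted, and the closeness, age and gender of named friends. An age or gender difference would point to different friends being named, while a closeness difference could reflect selection or altered rating;
   - report possible arm-dependent nomination as a limitation, since the count protects the size of the denominator but not who is in it.

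The analysis steps use items the survey already collects, need no further participants and leave the sample size unchanged.

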**Methods:**

This study will use a 2-group randomized trial design to test the effectiveness of reimbursements for peer referral in a web-based cross-sectional peer network survey. Young people aged 16-18 years recruited through Instagram, Snapchat, and a survey panel will be randomized to receive either scaled group reimbursement (the experimental group) or fixed individual reimbursement (the control group). All participants will receive a reimbursement of Aus $5 (US $3.70) for their own survey completion. In the experimental group (scaled group reimbursement), all participants within a peer network will receive an additional Aus $5 (US $3.70) voucher for each referred participant who completes the study, up to a maximum total value of Aus $30 (US $22.20) per participant. In the control group (fixed individual reimbursement), participants will only be reimbursed for their own survey completion. Participants’ peer networks are assessed during the survey by asking about their close friends. A unique survey link will be generated to share with the participant’s nominated friends for the recruitment of secondary participants. Outcomes are the proportion of a participant’s peer network and the number of referred peers who complete the survey. The required sample size is 306 primary participants. Using a multilevel logistic regression model, we will assess the effect of the reimbursement intervention on the proportion of primary participants’ close friends who complete the survey. The secondary aim is to determine participant characteristics that are associated with successfully recruiting close friends. Young people aged 16-18 years were involved in the development of the study design through focus groups and interviews (n=26).

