### Intervention

All primary and secondary participants will receive Aus $5 (US $3.70) as reimbursement for their own survey completion. Primary participants will be randomized to either (1) scaled group reimbursement (experimental) or (2) fixed individual reimbursement (control). In the scaled group reimbursement, all participants within a peer network (ie, the primary participant and all secondary participants) will receive an additional Aus $5 (US $3.70) voucher for each added secondary participant that the primary participant recruits to the study, up to a maximum total value of Aus $30 (US $22.20) per participant. The reimbursement per participant stops increasing at 6 per peer group, but up to 11 people in a peer group can be referred and reimbursed up to Aus $30 (US $22.20) each (1 primary and 10 secondary). In the fixed individual reimbursement, all participants will only be reimbursed Aus $5 (US $3.70) for their own survey completion. Table 1 describes the reimbursement amounts for participants in each group depending on the number of secondary participants who complete the survey within their friendship group.

**Table 1 table1:** Reimbursements for each intervention group.

Number of participants in friend group who complete survey	Reimbursement value per participant	
	Scaled group reimbursement (experimental)	Fixed individual reimbursement (control)
1 primary; 0 secondary	Aus $5 (US $3.70)	Aus $5 (US $3.70)
1 primary; 1 secondary	Aus $10 (US $7.40)	Aus $5 (US $3.70)
1 primary; 2 secondary	Aus $15 (US $11.10)	Aus $5 (US $3.70)
1 primary; 3 secondary	Aus $20 (US $14.80)	Aus $5 (US $3.70)
1 primary; 4 secondary	Aus $25 (US $18.50)	Aus $5 (US $3.70)
1 primary; 5-10 secondary	Aus $30 (US $22.20)	Aus $5 (US $3.70)

Reimbursements are in the form of a gift voucher sent by SMS to participants’ mobile numbers using a third-party service provider at the end of the trial period. However, due to the procedures of Student Edge, primary participants recruited through this setting will receive the initial Aus $5 (US $3.70) reimbursement on survey completion through Student Edge and further reimbursements via SMS at the end of the study, if applicable.

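### Absence of contact does not justify leaving researchers unblinded when completions are linked to nominated friends by initials or codename and only the scaled arm pays the group for extra completions

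*Protocol article*

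**What the plan says.** **Blinding.** Under Allocation of Intervention, the protocol article states: "Researchers will not be blinded to the intervention group as they have no direct contact with the participants". No other reason is given.

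**Outcome and unit of analysis.** Under Outcomes: "The primary outcome is defined as the proportion of primary participants’ close friends who complete the survey". Under Statistical Analysis, the model works at the level of the nominee: "Each close friend nominee can either be successfully recruited or not recruited (a binary outcome". A completion therefore has to be assigned to one particular nominee before it enters the model.

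**Linkage.** Under Data Management, the auto-generated URL links people within a peer network, and then: "Secondary participants’ survey data will be linked to the primary participants’ reported data using codenames and initials". Recruitment describes one URL per primary participant and friendship group, not one per nominee. Ethics Approval says that primary participants do not supply their friends' email addresses or mobile numbers.

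**Payment.** Under Intervention, everyone in a scaled-arm network, secondary participants included, gains Aus $5 for each added secondary participant, up to Aus $30 per person. In the fixed arm each person receives Aus $5 for their own survey and nothing for anyone else's.

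**Safeguards.** REDCap blocks repeat email addresses and mobile numbers (Recruitment), and entry needs a code sent to the participant's mobile (Data Collection).

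**The concern.** Lack of contact answers one question: could researchers who know the arm change how participants behave? It leaves another open: could knowledge of the arm, or a difference between the arms in who uses the link, affect which nominees are scored as recruited? Clicking the submit button is objective. Deciding that the person who clicked is a given nominee is less so, because several people can share initials and the codename is chosen by the primary participant.

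The exposure is not the same in both arms. Scaled-arm members gain when another person completes through the group's URL, and fixed-arm members do not. The safeguards stop one person from entering twice, but they do not stop a different, real person who was never nominated. If such a person is matched to a nominee, the scaled arm is credited with a close friend it did not recruit, and the error favours the trial's hypothesis. The Introduction itself reports that an earlier web-based referral study found participants inflating their referrals for payment.

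**Working it through.** **1. The chain from survey to outcome.**
- The nominee is the unit scored (Statistical Analysis).
- The URL identifies the group, not the nominee (Recruitment, Data Management).
- Within the group, only initials or a codename are named as the link (Data Management), with no contact identifiers to confirm it (Ethics Approval).
- Those holding the data know the arm (Allocation of Intervention).
- Another person's completion is rewarded in one arm only (Intervention, Table 1).

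Nothing in this chain is protected by the absence of contact with participants.

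**2. Reproducing the planned sample size.** Inputs from Sample Size: 0.2 per nomination in the scaled arm, a 2-fold difference (hence 0.1 in the fixed arm), 80% power, ICC 0.5, mean cluster size 3, coefficient of variation 0.83. Alpha is not stated; two-sided 0.05 is assumed.
- Unclustered: [1.96 × √(2 × 0.15 × 0.85) + 0.842 × √(0.2 × 0.8 + 0.1 × 0.9)]² / 0.1² = 199 nominations per arm.
- Design effect: 1 + (3 − 1) × 0.5 = 2, so 199 × 2 / 3 = 132.7 clusters.
- Relative efficiency for unequal clusters: L = 3 / (3 + 0.5/0.5) = 0.75, and 1 − 0.83² × 0.75 × 0.25 = 0.871.
- 132.7 / 0.871 = 152.3, rounded up to 153, as stated.

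The sample size is not in dispute. It corresponds to 153 × 3 × 0.871 / 2 = 199.9 effective nominations per arm.

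**3. Expected completions.** Scaled arm: 153 × 3 × 0.2 = 91.8. Fixed arm: 153 × 3 × 0.1 = 45.9. Apparent ratio: 2.0. (The article's own 92 is a total over both arms, consistent with 306 × 3 × 0.1 = 91.8, so it is a different quantity.)

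**4. Effect of false matches on the ratio** (shares assumed, none in the fixed arm).
- 10% of scaled-arm completions false: 91.8 × 0.9 / 45.9 = 1.8, seen as 2.0.
- 20% false: 91.8 × 0.8 / 45.9 = 1.6, seen as 2.0.

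**5. Effect on type I error.** Take a true rate of 0.10 in both arms, false matches in the scaled arm only, and a normal approximation with 199.9 effective nominations per arm.

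| False matches per nomination | Number among 459 nominations | Two-sided rejection rate |
|---|---|---|
| 0 | 0 | 5.0% |
| 0.01 | about 5 | 6.2% |
| 0.02 | about 9 | 9.8% |
| 0.05 | about 23 | 32.7% |

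The article gives no false-match rate, so this range is an assumption.

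**6. Cost of stricter matching.** Suppose a strict rule loses 10% of true friends in both arms (assumed). The rates become 0.2 × 0.9 = 0.18 and 0.1 × 0.9 = 0.09. The ratio stays at 2.0, and power under the same approximation falls from 80.2% to 75.1%.

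**The case against.** The strongest reply is that the plan already protects the primary outcome. The nominee is the unit, so a link user who matches nobody has no row in the model, and forwarding the link does not by itself bias anything. The number of close friends is also given before the arm is disclosed, which protects the denominator. This stands, and it narrows the point: bias in the primary outcome needs a false match to a specific nominee.

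Several stronger readings are tempting, but the article does not support them.

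- *Researchers judge which entries are false or duplicate.* No such step is described. REDCap detects repeat contact details and stops those people. Nor does the article say whether the linkage is done by a person or a program.
- *Up to 10 link users are accepted however many friends were nominated.* The text that "up to 11 people in a peer group can be referred and reimbursed" is a ceiling. Participants and Eligibility defines secondary participants as nominated and referred, and Data Collection ties the range of 0 to 10 to nominated friends. No check is shown when the link is opened, but silence in a condensed article is not a rule to admit anyone.
- *The second outcome is defined in two conflicting ways.* The abstract has "the number of referred peers who complete the survey", while Outcomes has "The secondary outcome is the number of close friends who complete the survey per primary participant". The research questions and Statistical Analysis also say close friends, so the abstract is best read as shorthand.

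It can also be said that matching rules belong in a full protocol or analysis plan. That is fair, and the absence of a matching manual is not the complaint. The complaint is the reason given for not blinding, which does not cover the linkage.

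**Conclusion.** The point holds as a risk of bias in a stated design choice. The reason given for leaving researchers unblinded does not reach the linkage step, the identifiers used there are weak, and the incentive that could produce false matches exists in one arm only. The likely direction is toward the hypothesis.

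The size cannot be known from the article. If 10% of about 92 scaled-arm completions were false matches and none in the fixed arm, a true ratio of 1.8 would appear as 2.0. With no true effect, about 9 false matches among 459 scaled-arm nominations would take the type I error from 5% to 9.8%. Both figures assume contamination in the scaled arm alone and the planned rates; some in the fixed arm would reduce them. A reader might infer that the trial's result is inflated, but nothing in the article shows that this occurred, and accurate matching would leave no such bias. The change is worth making because it costs little and, when the article was written, recruitment was complete but analysis had not begun.

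**What to change.** - Carry out the nominee linkage on a file from which arm and payment have been removed, before any analysis.
- Use one written rule for both arms: initials or codename, with age and gender agreeing. Primary participants already report each friend's age and gender (Data Collection). The rule should be checked against what the secondary participants' own records hold.
- Lock the linked file, then merge arm back.
- Score as recruited only nominees matched by that rule, and apply the same definition to the secondary count of close friends.
- Report link users matched to no nominee, by arm.
- Replace the sentence on blinding with a statement that linkage was done without knowledge of the arm.

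Masking removes any leniency that differs by arm. It does not remove a chance match when more non-nominated people use the link in one arm, which is why the agreement on age and gender and the count of unmatched users are both needed.

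The cost is a short data-handling step with no new data collection. Some true friends whose codenames cannot be matched will be lost in both arms, with some loss of power (to about 75% if the loss were 10% in each arm).
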